### Diet intervention

For both diets, food bags are delivered weekly by a home food delivery chain and make up approximately 50% of the daily intake during 5 weekdays. All meals are easily prepared with minimal peeling and cutting that could be challenging during active phases of RA. The meals are varied in style and ingredients to promote compliance and to ensure satisfactory nutrient intake. Participants in both groups are provided with recipes and information on the diet they are to follow. All participants are encouraged to maintain weight stability. Macronutrient composition of both diets is presented in Table 1.

**Table 1 Tab1:** Macronutrient content of the two intervention diets in ADIRA

	Fiber diet		Protein diet	
Macronutrient	Content	% of total energy	Content	% of total energy
Energy (kJ)	4623		4596	
Energy (kcal)	1105		1098	
Carbohydrate (g)	119	48	129	49
Protein (g)	46	17	62	23
Fat (g)	44	35	34	28
SFA (g)	12	9	16	13
MUFA (g)	14	11	11	9
PUFA (g)	14	11	11	3
Omega 3 (g)	4	3	0.8	0.6

*SFA* saturated fatty acids, *MUFA* mono saturated fatty acids, *PUFA* poly-unsaturated fatty acids

The anti-inflammatory diet bag contains 5 main meals, 5 breakfasts and 5 in-between-meal snacks per week: main meal dishes includes fish 3–4 times weekly, mainly oily fish, and 1–2 vegetarian meals rich in prebiotics (dietary fiber). Breakfast meals consist of low-fat dairy products, whole grains, nuts, berries and probiotic fruit juice is included with each breakfast meal. In-between-meal snacks comprise of 2 fruits per day. Participants are also provided with olive/rapeseed oil for cooking. Wholegrain, legumes and vegetables ensure an adequate intake of fiber and prebiotics, and fish, oils and nuts provide unsaturated and LC n-3 PUFA and probiotics are added to the diet. Participants are not provided with any meat and are encouraged to restrict intake of red meat to 3 servings per week. This diet therefore combines components of a vegetarian and Mediterranean diet with LC n-3 PUFA and probiotics, which all have shown promising effects on clinical outcomes of RA. Total content from animal sources (fish and low fat dairy products) is 28% and from vegetable sources 72%. In an effort to blind the intervention to participants, this bag is referred to as *the fiber bag* instead of anti-inflammatory bag.

The control diet bag contains 5 main meals, 5 breakfasts and 5 in-between-meal snacks per week: five dishes including meat or chicken. The 5 servings of breakfast meals consist of full-fat dairy products, corn flakes, white bread and fruit juice without probiotics. In-between-meal snacks comprise of curd and protein bars. Participants will also be provided with a mix of butter and margarine for spread, together with recipes and instructions for food preparation. To blind the intervention to participants, this bag is referred to as *the protein bag*. Protein content is not unusually high; it is actually similar to the reported intakes of Swedish men and women between the ages of 45–65 years in the national dietary survey Riksmaten 2010 in terms of macronutrients and quality of fat and carbohydrate intake [20]. Thus, the diet is representative of the dietary habits of the average Swedish person. Total content from animal sources (beef and chicken) is 48% and from vegetable sources 52%. In Sweden, high protein and full fat products rich in saturated fat (e.g, butter) have been trendy during the last years and it is not obvious to most participants which diet is the healthy one. Also, they are informed that the effects of two different diets are evaluated in the study.

Participants expressing dislike of a certain food item have the possibility to exchange this for a food item of similar nutrient composition.

### Analysis of outcome

Outcomes are measured after each diet regimen. Primary outcome is DAS28, where we expect a difference between diet regimens > 0.6 units (considered clinically relevant) in the intention-to-treat analysis. Secondary outcomes include DAS28-CRP (where hs-CRP is used instead of ESR in the DAS28 calculation), inflammation markers, anthropometry, QoL, HAQ, blood lipids, blood pressure, acute health care visits and NSAID and corticosteroid consumption. Differences in outcomes will be compared for the two diet regimens in ANCOVA analyses, adjusting for baseline disease activity scores and potential confounders (e.g., age, other lifestyle factors). Mixed models also will be applied to fully handle missing data. Interaction by sex and socio-economic position will be evaluated.

Drop-outs will be included in secondary analyses of changes in DAS28 within one diet period if they have completed at least one diet period. Drop-out analyses will be carried out in that baseline information will be compared between drop-outs and those who complete the study.

Data will be entered and stored at the Dept Internal Medicine and Clinical Nutrition, Sahlgrenska Academy, University of Gothenburg, Sweden. Stored data files will not contain any personal identifying information; only the PI will have the code list and this will be kept in a locked drawer. Quality control procedures of data will be carried out by the PI. All members of the research team have access to final trial dataset. Results will be published in international peer-reviewed journals. They will also be shared with professional societies in rheumatology and nutrition. Participants will receive information about their own results at the end of the trial.

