Thereafter, patients were randomized to either diet regimen for 10 weeks. Randomization scheme was computer-generated and revealed to participants and study team at the baseline visit. At the end of the 10 wk. period, the same measurements are repeated. Individual pharmacological treatment is reported at baseline and any changes or additions in pharmacological treatment are noted during the study period. After a 2–3-mo wash-out period, the alternative diet regimen is followed for another 10 weeks. Compliance to the diets is monitored by a telephone administered interview at wk. 5 in both diet periods and with analyses of plasma phospholipid LC n-3 PUFA at the end of each diet period as well as with 3 d food record at the end of each diet period. Support for participants is provided at this telephone interview to promote trial retention; it is also possible for participants to contact the study team at any time during the intervention. Participants are asked to report any side effects. Should a participant decide to quit the trial, no further data are collected.

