### Sample size

To detect a DAS28 difference of 0.6 units (clinically relevant) with 90% power and α = 0.05, 38 patients are needed in cross-over design. Skoldstam [13] detected a difference of 0.6 units with 30 patients per group in a diet parallel trial. We have carried out a pilot cross-over diet study that detected a difference of 0.34 units with 23 patients, confirming that cross-over design reduces the sample size (unpublished results). To account for drop-out or non-compliance, ADIRA cross-over study included 50 women and men.

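### The primary DAS28 contrast is labelled intention-to-treat, but the stated handling of drop-outs does not fit that label, whichever of the two planned models is primary

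*Protocol article*

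**What the plan says.** All but one of the relevant statements are in the protocol article under Analysis of outcome.

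- Label: for DAS28, "we expect a difference between diet regimens > 0.6 units (considered clinically relevant) in the intention-to-treat analysis".
- Main method: "Differences in outcomes will be compared for the two diet regimens in ANCOVA analyses, adjusting for baseline disease activity scores and potential confounders".
- Missing data, in the next sentence: "Mixed models also will be applied to fully handle missing data".
- Drop-outs, in the next paragraph: "Drop-outs will be included in secondary analyses of changes in DAS28 within one diet period", provided that at least one diet period was completed. A baseline comparison of drop-outs with completers is also planned.

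The remaining rule is at the end of the follow-up description under Participant selection: "Should a participant decide to quit the trial, no further data are collected".

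Under Sample size, 38 patients are required and 50 were included. The difference is to cover drop-out or non-compliance.

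**The concern.** An intention-to-treat contrast should account for everyone randomized. Here the label, the place given to drop-outs and the data-stop rule are each stated outright, and they do not fit together. This is a conflict between stated rules, not detail left to a fuller plan.

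What is at stake is the primary estimate and what it may be called. Participants are only partially blinded, and the article itself expects disease activity and medication to vary over time. Quitting could therefore plausibly be related to how a participant is doing on a given diet. If it is, a contrast among those who finish both diets can differ from the contrast for all randomized, and readers would take it for the latter.

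**Working it through.** **1. Who contributes to what, following the text**

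| Participant | End-of-period DAS28 | Within-patient ANCOVA of the two diets | Mixed model | Drop-out sentence |
|---|---|---|---|---|
| Completes both periods | two | yes | yes | does not apply |
| Completes period 1, then quits | one | no | yes | secondary analysis |
| Quits during period 1 | none | no | no outcome to use | not included |

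**2. The two readings**

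- *ANCOVA primary.* This is the natural reading, because the mixed models are introduced as something applied in addition. Row 2 is then lost to the primary contrast, and the drop-out sentence agrees with that. The intention-to-treat label is wrong.
- *Mixed model primary.* Row 2 enters the primary estimate. The sentence that assigns row 2 to secondary analyses is then in conflict with the model.

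Row 3 has no outcome under either reading. No model *fully* handles that. A likelihood-based mixed model is valid under missing at random and cannot recover values that the plan does not collect.

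**3. The plan's own figures**

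The cross-over formula is n = ((z₀.₉₇₅ + z₀.₉₀) × SD_diff / δ)². No SD is given, so 38 cannot be reproduced forwards. Solved backwards (two-sided 5% assumed), SD_diff = 0.6 × √38 / (1.960 + 1.282) = 1.14, or 1.11 with the paired t version. The margin is 50 − 38 = 12, which is 12/50 = 24%. It covers drop-out *or* non-compliance, so 12 lost outcomes is an upper case.

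**4. Illustration of size (assumption: no diet effect in those who leave)**

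All-randomized difference = 0.60 × (50 − d)/50 for d drop-outs. The power column takes 50 analysed and the back-solved SD_diff of 1.11.

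| d | All-randomized difference | Power |
|---|---|---|
| 0 | 0.60 | 96% |
| 3 | 0.60 × 47/50 = 0.56 | 94% |
| 6 | 0.60 × 44/50 = 0.53 | 91% |
| 9 | 0.60 × 41/50 = 0.49 | 87% |
| 12 | 0.60 × 38/50 = 0.46 | 81% |

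**5. Would the mixed model be enough?**

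A simulation with 50 participants and a true effect of −0.60 (a reduction in DAS28) assumed a between-patient SD of 0.8 and a within-patient SD of 0.785, which gives SD_diff = 0.785 × √2 = 1.11.

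| Assumed drop-out mechanism | Lost | Completers | Mixed model |
|---|---|---|---|
| After period 1, depending on the observed DAS28 | 14% | −0.58 | −0.60 |
| While doing badly on the fiber diet, that outcome never collected | 18% | −0.72 | −0.76 |

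In the first case the mixed model removes a small bias, with the same standard error (0.166). In the second it does not help and lies slightly further from the truth than the completer estimate. The SDs and both mechanisms are assumptions, not figures from the article.

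**The case against.** The strongest defence is that the text never says drop-outs go *only* into secondary analyses, and that a mixed model able to use one-period participants is already planned. A reader might infer that the primary result simply is a completer result. The documents do not establish that, because the primary model is not named. This part of the objection stands, and the point is conditional for that reason. It does not remove the conflict. A sentence that says where drop-outs are included, and on what condition, reads as the rule for handling them, and it fits badly with a primary mixed model that already contains them.

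Three further objections also stand in part.

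- The data-stop rule concerns leaving the trial. A reader might infer that anyone who stops the diet is lost, but the article does not say so, and Sample size names drop-out and non-compliance separately. Stopping the diet and leaving the trial need to be distinguished. No error is shown for those who only stop the diet.
- Each completer supplies both diets, so a completer contrast is not biased by necessity. It depends on why people leave, which the article cannot know.
- A missing-not-at-random sensitivity analysis is ordinary analysis-plan content. Its absence from a condensed article is not a fault.

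The defence cannot save the word *fully*, which is wrong for any mixed model.

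**Conclusion.** The point holds as an inconsistency between stated rules. The intention-to-treat label fails if the ANCOVA is primary. If the mixed model is primary, the drop-out sentence has to be reconciled with it. The missing-data claim is too strong in either case.

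The size is not known from the documents. On the assumption that leavers have no diet effect, the gap between completers and all randomized runs from 0.04 DAS28 units with 3 drop-outs (0.60 − 0.56) to 0.14 with 12 (0.60 − 0.46). The upper end requires every participant in the margin to be lost to follow-up, which the article does not predict. If loss depends only on observed DAS28, the simulated bias among completers is about 0.02. Because the primary estimate and its label are affected and the remedy is cheap, this should be settled before analysis.

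**What to change.** 1. Under Analysis of outcome, name as primary one mixed model on all randomized participants that uses every available end-of-period DAS28, including those with a single completed period. Keep the complete-pair ANCOVA as a sensitivity analysis, and reword the drop-out sentence to match. State that participants with no end-of-period value contribute no outcome.
2. Under Participant selection, say that participants who stop the diet without withdrawing consent are still asked to attend the end-of-period visits already scheduled. Step 5 of the working shows why: changing the model does not repair outcomes that were never collected.
3. Replace the claim of full handling with *handle under a missing-at-random assumption*.

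A missing-not-at-random sensitivity analysis is optional and can be left to the SAP.

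The cost is protocol and SAP wording, a few retained visits, and possibly a slightly smaller estimate.

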### Cost-effectiveness

ADIRA is an efficacy study and hence not optimal for evaluation of cost-effectiveness in clinical use. Like in all lifestyle interventions, the long lasting compliance to lifestyle changes is essential for such evaluations and this will be evaluated in the following effectiveness ADIRA trial. However, it will still be possible to evaluate if the ADIRA efficacy trial has *potential* to be cost-effective in clinical praxis. The main cost is incremental costs of anti-inflammatory diet compared to control diet and these exist as long as the new diet is consumed, but also participants’ time spent will be recorded and valued. Expected benefits include gain in QoL and reduced use of acute health care and medication as well as sick leave. Gain in QoL (mainly pain relief, measured with SF-36/SF-6D [21–23], EQ-5D and EQ VAS [24]) likely occurs in short time and is thus possible to evaluate 10 weeks from start. In contrast, changes in health care use and sick leave may take longer to accrue. Therefore, the main economic analysis will be a comparison between incremental food costs and incremental QoL while the dietary change is in use. In practice, the food costs and QoL gain per week diet is used, presented as costs per quality-adjusted life-years (QALY). Best evidence of the effect of pain relief for RA patients on use of acute health care, medication and sick leave will be obtained from literature and used in evaluations of the cost-effectiveness of anti-inflammatory diet compared to control diet.

### Sample size

To detect a DAS28 difference of 0.6 units (clinically relevant) with 90% power and α = 0.05, 38 patients are needed in cross-over design. Skoldstam [13] detected a difference of 0.6 units with 30 patients per group in a diet parallel trial. We have carried out a pilot cross-over diet study that detected a difference of 0.34 units with 23 patients, confirming that cross-over design reduces the sample size (unpublished results). To account for drop-out or non-compliance, ADIRA cross-over study included 50 women and men.

### Metabolomics

For metabolomics, serum samples will be analyzed with nuclear magnetic resonance (NMR) at the Swedish NMR Centre at University of Gothenburg, Sweden, as well as with mass spectrometry (MS) at Chalmers Technical Institute, Gothenburg, Sweden. We will use an untargeted metabolomics approach for a global description of the metabolites that can be found in participants’ serum using unsupervised statistical analyses, ie principal component analysis (PCA). Subsequently supervised clustering, ie orthogonal projection to latent structures-discriminant analyses (OPLS-DA [25]) and OPLS-EP [26] (for paired data) will be performed to compare metabolites between patients who respond and who don’t respond to the inflammatory diet. Finally, in a targeted metabolomics approach, metabolites providing the greatest discrimination between groups of responders vs. non-responders will be identified using publicly and commercially available as well as in-house developed databases.

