**Methods:**

In total, 50 RA patients with moderate disease activity are randomized to receive initially either a portfolio diet based on several food items with suggested anti-inflammatory effects or a control diet during 2 × 10 weeks with 3 months wash-out between diets. Food bags are delivered weekly by a home food delivery chain and referred to as the fiber bag and the protein bag, respectively, to partially blind participants. Both groups continue with regular pharmacological treatment. Known food biomarkers will be analyzed to measure intervention compliance. Impact on disease severity (measured by DAS28, a composite score which predicts disability and progression of RA), risk markers for cardiovascular disease and quality of life are evaluated after each diet regimen. Metabolomics will be used to evaluate the potential to predict responders to dietary treatment. A health economic evaluation is also included.

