Whether patients with RA respond to a dietary intervention or not might relate to genetics, habitual diet, the microbiome and/or the diversity and intensity of disease activity. Metabolomics, ie the analysis of low molecular weight metabolites, investigates overall metabolomic activity, taking genetic and environmental variation into account. It is a powerful tool to measure global and dynamic metabolic responses in disease and clinical intervention and some research also exist on RA. Different baseline metabolic profiles have been identified among patients with active RA compared to those in remission [16]. Thus, it may be possible to identify metabolic biomarkers to predict response also to dietary treatment among patients with RA. The metabolomics methods are relatively new and therefore few dietary interventions have used this approach to look at metabolic effects. Further, since the metabolism might be pertubated in patients with RA due to the metabolic syndrome or cachexia, metabolomics opens new possibilities to look at previously unknown metabolic changes as a consequence of a specific diet.

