### Research objective and specific questions

We hypothesize that an anti-inflammatory diet, in addition to pharmacological treatment, can improve health and quality of life in patients with rheumatoid arthritis. Specific questions are if an anti-inflammatory diet, compared to a usual Swedish diet, can reduce inflammation, pain and disease activity; reduce risk markers of cardiovascular disease; improve body composition; improve quality of life; reduce patient and societal costs related to the disease, and if metabolomics can be used to predict responders.

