### Participant selection

Invitation letters to the study were sent to patients with RA residing in the Västra Götaland region, Sweden, identified through the Swedish Rheumatology Quality Register, SRQ (http://srq.nu/). Responders to the invitation letters or to posters at the Sahlgrenska University Hospital were invited to screening visits. Inclusion criteria was disease duration > 2 years, active disease i.e. DAS28 ≥ 2.6 that was clinically stable and under adequate control and medication at the screening visit. DAS28 stands for Disease Activity Score, where swelling and tenderness in 28 different joints are evaluated in combination with information on erythrocyte sedimentation rate (ESR) as well as patient-reported global assessment of health [18]. Exclusion criteria included other condition demanding active medical attention, changes in DMARD during last 8 weeks, intolerant or allergic to food items included in the intervention diets or not willing to eat omnivore diet. Between February and September 2017, 13 men and 53 women, 18–70 years of age, were screened for eligibility. At the screening visit, study details were presented, informed consent obtained and habitual diet was assessed. All ADIRA study visits take place at the research ward of the Clinical Rheumatology Research Centre, Sahlgrenska University Hospital, Gothenburg, Sweden, and measurements are carried out by two registered nurses experienced in rheumatology assessments along with the project team.

Patients agreeing to participate and fulfilling all inclusion criteria were thereafter invited to baseline measurements within a few weeks. These included clinical phenotype, body composition (bioelectric impedance spectroscopy) and health assessment, 3 day food record, serum samples for blood lipids, urine sample, metabolomics and inflammation markers (e.g., high-sensitive C-reactive protein (hs-CRP), cytokines and intercellular adhesion molecules), Health Assessment Questionnaire [19] (HAQ), Quality of Life (QoL) and a questionnaire on socio-demographics, lifestyle, acute health care visits and non-steroidal anti-inflammatory drugs (NSAID) and corticosteroid consumption.

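### The metabolomics aim is to predict responders, but the responder comparison includes a paired method that needs post-diet samples, and metabolite selection is not limited to pre-diet samples

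*Protocol article*

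**What the plan says.** The aim is prediction. The abstract's Methods paragraph states: "Metabolomics will be used to evaluate the potential to predict responders to dietary treatment". The section on the research objective and specific questions lists one metabolomics question: "if metabolomics can be used to predict responders". The Background argues for this from profiles measured at baseline ("Different baseline metabolic profiles have been identified among patients with active RA compared to those in remission") and concludes that "it may be possible to identify metabolic biomarkers to predict response also to dietary treatment". The Background also gives a second interest: "metabolomics opens new possibilities to look at previously unknown metabolic changes as a consequence of a specific diet". That interest does not reappear among the specific questions.

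On sampling, Participant selection lists among the baseline measurements "serum samples for blood lipids, urine sample, metabolomics and inflammation markers". It says that the same measurements are repeated when the 10-week period ends, and then: "After a 2–3-mo wash-out period, the alternative diet regimen is followed for another 10 weeks".

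On analysis, the Metabolomics section starts with unsupervised PCA. The supervised step follows, with OPLS-DA and "OPLS-EP [26] (for paired data) will be performed to compare metabolites between patients who respond" and those who do not. The last step identifies the metabolites that separate the two responder groups most strongly. The section does not say which time point enters which model. The Strengths section later describes the product as biomarkers of response to the intervention.

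**The concern.** A predictor of response must be measurable before the diet starts. A paired method uses repeated samples from one patient, and the sample taken at the end of the fiber diet comes from the same set of measurements as the DAS28 that would show whether the patient responded. A metabolite that shifts because disease activity fell will separate responders from non-responders, yet may say nothing about who would respond.

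The selection rule adds to this. It ranks metabolites by how well they discriminate, and markers that move with the outcome are likely to rank high. A list chosen this way could look strong and still be of no use for choosing patients before dietary treatment, which is the question the article asks.

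**Working it through.** The article gives no figure to reproduce on this point. The check is a side-by-side reading, followed by an illustration of size.

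**Step 1: what the aim requires.** The abstract and the specific questions ask about predicting responders, and the Background rests this on baseline profiles. The predictor sample must therefore predate the anti-inflammatory (fiber) diet.

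**Step 2: what paired can mean.** Responders and non-responders are different patients, so they cannot form the pairs. The pairs must be two samples from one patient: before versus after a diet, or after one diet versus after the other.

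**Step 3: which samples the schedule offers.** The text places metabolomics samples at baseline and at the end of each diet period.
- *Fiber-first patient:* study baseline is the only sample before the fiber diet, so any pair includes a sample taken after it.
- *Control-first patient:* a pair wholly before the fiber diet is conceivable, but one of its samples follows the control diet, and fiber-first patients have no matching pair.

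Every pair thus contains at least one post-diet sample, and a paired analysis covering all patients must use samples taken after the fiber diet.

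**Step 4: whether selection separates the two uses.** The last step takes the metabolites that discriminate best between the responder groups. It does not restrict them to a pre-diet model or distinguish the OPLS-DA results from the OPLS-EP results.

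**Step 5: illustration of size, all inputs assumed.** Responders were defined by a median split of DAS28 change. The metabolites had baseline values unrelated to response, and their change on diet correlated with DAS28 change at rho. Each was tested with a two-sample t-test at 0.05, over 400 runs. The two sample sizes are the 38 patients needed and the 50 included, from the Sample size section. The table gives the share of these non-predictive metabolites that was flagged.

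| n | rho | Baseline samples | Paired change |
|---|---|---|---|
| 38 | 0 | 4.9% | 4.9% |
| 38 | 0.3 | 4.5% | 31.1% |
| 38 | 0.5 | 5.1% | 71.4% |
| 38 | 0.7 | 5.0% | 98.2% |
| 50 | 0 | 5.0% | 5.2% |
| 50 | 0.3 | 5.2% | 40.0% |
| 50 | 0.5 | 5.4% | 85.1% |
| 50 | 0.7 | 5.2% | 99.7% |

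On baseline samples the rate stays near the nominal 5% whatever rho is. On paired change it rises with rho.

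**The case against.** The strongest reply is that this is silence in a condensed article, not an error. Which serum sample enters which multivariate model is detail that a full protocol or analysis plan would normally hold. The Metabolomics section does not itself use the language of prediction. The Background gives metabolomics a second, legitimate purpose, the study of metabolic change caused by diet. A natural reading would then be OPLS-DA for discrimination between patients and OPLS-EP for change within patients. The last step may mean no more than chemical annotation of discriminating signals from databases.

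Part of this stands. OPLS-DA on baseline samples is fully open under the text and would be a valid prediction analysis. Comparing metabolic change between responders and non-responders is a reasonable mechanistic analysis. Nothing says that the two models are pooled. The simulation builds in a correlation between changes and then detects it, with t-tests in place of OPLS, so it shows the mechanism and not the size to expect in this trial.

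What does not stand is the claim that nothing was fixed. The article makes a positive choice: it ties the paired method to the responder comparison, while the only listed question is prediction. The second purpose in the Background is not the contrast to which OPLS-EP is assigned. Nor does it matter that the pairing may be fiber versus control instead of before versus after, because both contain post-diet samples.

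**Conclusion.** The point holds as a mismatch between the stated question and one of the methods named for it, made worse by a selection step that does not distinguish pre-diet from post-diet information. Metabolites that change with the DAS28 response could be selected as if they predicted it. This is a risk to an exploratory objective. The DAS28 primary analysis is unaffected.

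The conclusion rests on pairing within patients and on the sampling described in the text. The size depends on how closely metabolite change follows DAS28 change, which the article does not give; the table in the working is illustrative only.

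Two stronger readings are not supported:
- A reader might infer that the prediction question will be answered with markers of the outcome. The article does not say that post-diet metabolites will be reported as predictors, and a baseline OPLS-DA remains available.
- A reader might infer that control-first patients will have an outdated predictor sample, because study baseline precedes their fiber diet by a whole control period and the wash-out. The article does not say that study baseline serves as the pre-diet sample for them. The schedule figure, which could show a sample at the start of the second period, is not available here.

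**What to change.** State in the Metabolomics section, or in the analysis plan, that predictive metabolites are fitted and selected only from an OPLS-DA model on samples drawn before the fiber diet. Use the sample taken at the start of that diet period where one exists, and otherwise study baseline with sequence accounted for. Report OPLS-EP separately, as a description of metabolic change on the diet, which serves the second interest in the Background. Metabolites found only through OPLS-EP should not be called predictors.

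This changes analysis wording only. The downside is that fewer metabolites are likely to discriminate, because those that merely move with the response no longer count.
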